### Variables of the study

#### Primary outcome variables

Proportion of ANC service use

Proportion of institutional delivery

#### Secondary outcome variables

Proportion of PNC service use

Pregnancy outcome

#### Independent variables

Mobile-phone-based voice message

Socio-demographic characteristics (covariate)

Maternal health status (covariate)

### Operational definitions

*Mobile-health* **=** the use of a mobile phone to support health care at individual, community or systems level*Maternal health care service utilization* **=** the women’s health care service use from conception to delivery and during postnatal period till 45 days or 6 weeks*Antenatal care service use* **=** maternal health care service use during pregnancy*Institutional delivery* **=** giving birth in health facilities*Postnatal care service use* = maternal health service use after birth within 45 days*Pregnancy outcome* ***=*** the final result of a fertilization event such as live birth (full-term or preterm birth), stillbirth, spontaneous abortion and induced abortion*Adverse pregnancy outcome* = includes maternal adverse outcomes and/or neonatal adverse outcomes*Maternal adverse outcome* = maternal illness or maternal near miss and/or maternal death*Neonatal adverse outcome* = neonatal morbidity and/or neonatal mortality*Stillbirth* **=** any fetus born at 28 weeks of gestational age or more with no heart beat or respiratory effort*Low birth weight* **=** birth weight less than 2500 g after viability*Preterm* **=** any birth occurring between 28 and 37 weeks of gestation*Abortion* **=** the termination of pregnancy before 28 weeks of GA*Maternal near miss* **=** a woman who nearly died but survived a complication that occurred during pregnancy, childbirth or within 45 days of termination of pregnancy*Maternal mortality* **=** the death of women during pregnancy or within 45 days of termination of pregnancy irrespective of the duration from any cause related to, or aggravated by, the pregnancy or its management but not from accidental or incidental causes*Neonatal mortality* **=** the death of infants with in the first 28 days of life*Institutional delivery* = child-birth attended by skilled health professionals*Maternal under-nutrition* **=** mother will be considered as undernourished if she has anemia and/or wasting or/and underweight or low weight-gain during pregnancy*Anemia* **=** mother will be considered as anemic if the level of hemoglobin is less than 11 g/dl which will be measured through the Hemocue machine*Severe anemia* = mother will be considered to have severe anemia if the level of hemoglobin is less than 7 g/dl which will be measured through Hemocue machine*Wasting* = mother will be considered to have wasting if the MUAC measurement is less than 18.5 cm*Underweight* = mother will be considered as underweight if her Body Mass Index (BMI) is less than 18.5 kg/m^2^

#### Outcome measures

The baseline characteristics of the study participants in both intervention and control groups will be compared with those of the general population. During baseline assessment, socio-demographic characteristics, eligibility criteria (pregnancy with less than 16 weeks of GA, ownership of a mobile phone and willingness to participate) and maternal health conditions, Nutritional status and previous maternal health care use experiences will be assessed.

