### Study setting

This study will be done in Haramaya and Kombolcha districts, which are in Eastern Haaraghe Zone, Oromia Regional State, Eastern Ethiopia.

Haramaya district, which is about 506 km from Addis Ababa, the capital city of Ethiopia, is located between 9°24′N and 42°01′E and is 1400–2340 m above sea level. According to the 2007 national census of the country, its population was 271,018, of whom 48.97% were women and 18.46% were urban dwellers. Moreover, by using pregnancy rate estimation factors of 4.6%, around 12,467 women are expected to be pregnant in this district. In the district, there are seven HCs, 22 HPs and one hospital, [14].

On the other hand, the district of Kombolcha is 540 km from Addis Ababa and is found at between 1200 and 2460 m above sea level. According to the 2007 national census report, its population was about 140,080, of whom 49.3% were women and 9.01% were urban dwellers. Moreover, by using pregnancy estimation factors of 4.6%, about 6444 women are expected to be pregnant in this district. In Kombolcha, there are five HCs and 22 HPs.

Related to study parameters, like socio-demographics, economic characteristics and maternal health care service coverage, the two districts have similarities [15].

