#### Phase I

In this phase, for both intervention and control groups, a baseline survey will be conducted on sociodemographic characteristics and maternal health care service use via a structured, interview-based questionnaire which will be adopted from similar studies. Maternal health status will be assessed through a medical interview checklist and nutritional status will be screened by using a mid upper-arm circumference (MUAC) tape, a weighing scale and a Hemacue machine or portable hemoglobin analyzers to test for hemoglobin level.

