### Statistical method

For primary and secondary outcomes, Relative Risk with 95% confidence interval will be estimated. The association of dependent and independent variables will be checked by using the chi-square test. For count data, further analysis will be done by using multivariate count data logistic regressions or the Poisson Regression Model will be used to examine the effect of treatment on trial arms and Kaplan-Meier survival analysis will be used to compare maternal health care service use over time among treatment and control groups. Moreover, to adjust for both the clustering effect of the districts with their respective HCs and the participant-level intracluster correction, Generalized Estimating Equation (GEE) models will be used. All the analysis will be done by using STATA software.

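### With one district and one health centre per arm, the only stated baseline comparison is with the general population, and previous maternal-care use is collected but not listed as a covariate for the primary relative risk

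*Protocol article*

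**What the plan says.** **Allocation.** Under Randomization and sampling procedure, Haramaya (intervention) and Kombolcha (control) are assigned by lottery. One health centre per district is then chosen purposively for power and network access, and 320 women per arm are drawn at random from eligible women in the surrounding kebeles. Women are randomly sampled within an arm; they are not randomly allocated to one.

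**Baseline comparison.** Outcome measures states: "The baseline characteristics of the study participants in both intervention and control groups will be compared with those of the general population". No other section states a baseline comparison.

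**Data collected.** Phase I says that "a baseline survey will be conducted on sociodemographic characteristics and maternal health care service use via a structured, interview-based questionnaire", in both arms. Outcome measures adds that "Nutritional status and previous maternal health care use experiences will be assessed".

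**Covariates.** Independent variables labels two groups as covariates: socio-demographic characteristics and maternal health status. Previous care use is not among them. Sub-group analysis names it as a factor for exploratory effect modification.

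**Primary analysis.** Statistical method says: "For primary and secondary outcomes, Relative Risk with 95% confidence interval will be estimated". It adds chi-square tests, multivariable or Poisson models for count data, and GEE models to account for clustering. No covariate is named for the primary relative risk.

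**Districts.** Study setting and the randomisation section call the districts similar. Study setting also reports that in Haramaya "48.97% were women and 18.46% were urban dwellers", and in Kombolcha "49.3% were women and 9.01% were urban dwellers". It lists a hospital for Haramaya and none for Kombolcha.

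**The concern.** When many units are randomised, a baseline table by arm is largely a check on chance. Here one district faces another, so any difference in case mix between two hand-picked catchments enters the comparison whole. The informative baseline question is how the two groups of women differ from each other. Comparing each with the general population answers a different question, that of representativeness.

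Previous antenatal and delivery care is a direct pre-treatment measure of the behaviour the trial tries to change, so it is an obvious candidate for adjustment. The protocol pays to collect it and then assigns it only to sub-groups. A sub-group analysis asks whether the effect varies with previous use; it does not correct the overall estimate for an imbalance in it. A clustering adjustment bears on the standard error and does not remove a difference in case mix either.

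At stake is whether part of the reported relative risk reflects who lived in the two catchments rather than the voice messages.

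**Working it through.** **1. The plan's own figures.** Inputs from the sample size sections: 47% against 60%, two-sided 5%, 80% power, design effect 1.3. The two-proportion formula gives 230 per arm, or 246 with continuity correction. 246 × 1.3 = 319.8, rounded up to 320, which matches. The planned effect is 60 − 47 = 13 points, a relative risk of 0.60/0.47 = 1.28. The sample size is not in dispute; these figures set the scale for what follows.

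**2. What the sections say together.**

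| Element | Stated | Effect on case-mix differences between arms |
|---|---|---|
| Lottery | 2 districts, 1 per arm | No expected balance between women |
| Baseline comparison | Each arm with the general population | Does not describe the difference between arms |
| Listed covariates | Socio-demographics, maternal health status | Not tied to the primary relative risk |
| Previous care use | Collected; sub-groups only | Not adjusted for |
| GEE | For clustering | Does not remove case-mix differences |

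**3. Size, using the one imbalance the document quantifies.** Let u_I and u_C be the urban shares, g the urban-rural gap in facility delivery, and r the rural rate, with no message effect. The control rate is r + u_C·g, set to 47%. The intervention rate is r + u_I·g. The spurious difference is (u_I − u_C)·g.

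- u_I − u_C = 18.46 − 9.01 = 9.45 points (ratio 2.05).
- g is not in the document. Assumed 20 points: 9.45 × 0.20 = 1.9 points, relative risk (47 + 1.89)/47 = 1.04.
- Assumed 30 points: 9.45 × 0.30 = 2.8 points, relative risk (47 + 2.835)/47 = 1.06.
- Wider range, g = 10 to 40 points: 0.9 to 3.8 points, relative risk 1.02 to 1.08.

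Against the 13-point target, 1.89/13 = 15% and 2.835/13 = 22%. If urban residence raises facility delivery, the direction favours the intervention arm.

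**4. The same formula for previous care use.** Every input here is assumed, because the document gives no figures by district. An imbalance of 5 to 20 points with an outcome gap of 20 to 40 points gives between 5 × 0.20 = 1 point and 20 × 0.40 = 8 points, or a relative risk of 1.02 to 1.17. This shows how the quantity scales; it is not an estimate for these districts.

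**5. What adjustment can reach.** Previous use and residence vary between women within a district, so a model can use them. The hospital is a property of the district. With one district per arm it coincides with treatment, and no individual covariate separates the two.

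**The case against.** The strongest reply is that much of this is silence in a condensed article. The sentence on the general population does not exclude a table by arm. Comparing a sample of phone owners from purposively chosen sites with the population has a legitimate use. The analysis plan also commits to CONSORT reporting, and a full covariate list commonly sits in a statistical analysis plan. This stands in part: it would be wrong to infer that the investigators have decided against a between-arm comparison. What remains is what the article does fix: one named comparator, a covariate list without previous use, and a sub-group role for previous use.

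Four stronger readings are tempting and are not supported.

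- *The primary relative risk will be unadjusted.* Two variable groups are labelled covariates, and multivariable models are mentioned, though for count data. The supportable statement is that no covariate is tied to the primary estimate.
- *Leaving out previous use lets the known district differences into the result.* The differences shown are urban share and the hospital. Residence plausibly falls under socio-demographic characteristics, which are listed. The hospital is beyond the reach of any individual covariate.
- *The arms differ in previous care use.* No such figures are given, and the document describes service coverage as similar.
- *The bias could approach the whole 13 points.* That needs a very large difference in urban share between the two catchments. The article gives no catchment figures, and both health centres were chosen for the same reason.

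**Conclusion.** The point holds in a limited form. The design gives no expected balance between women, the only stated baseline comparison does not compare the arms, and a collected predictor of the outcome has no stated role in adjusting the primary result. This is a weakness in the analysis as fixed, and it is worth correcting before enrolment.

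On the one documented imbalance, the illustrative bias is about 1.9 to 2.8 points, a relative risk of 1.04 to 1.06 at a 47% control rate, against a target of 13 points and 1.28. This rests on an assumed urban-rural gap of 20 to 30 points. It also takes whole-district 2007 census shares as standing for the enrolled women, who are phone owners from one catchment each. The true imbalance could be smaller or larger. The contribution of previous care use cannot be sized from the document. Adjustment would reduce case-mix differences; the confounding of district with arm would remain.

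**What to change.** - **Outcome measures:** state that baseline characteristics, including previous maternal-care use and urban or rural residence, will be tabulated by arm. The general-population comparison may stay, labelled as a check of representativeness.
- **Independent variables:** add previous maternal-care use as a covariate, with a separate category for women with no previous birth, and name residence explicitly.
- **Statistical method:** pre-specify a covariate-adjusted relative risk from a log-link or modified Poisson model. Include previous use, residence and the other socio-demographic and maternal-health covariates already listed, with the individual items fixed in advance. Report the unadjusted relative risk beside it.
- **Limit on covariates:** do not adjust the antenatal-care outcome for antenatal visits made by enrolment. Under Primary outcome measures a single visit counts as success, so a woman with such a visit has already met the outcome. Previous use should therefore mean use in earlier pregnancies.
- **Limitation:** state that adjustment can reduce differences in case mix but cannot remove district-level confounding, such as the hospital listed only for the intervention district.

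The cost is wording and minor programming. Previous use and socio-demographics are already in the Phase I survey, and Trial status says participant selection has not begun. The article gives only broad headings for the questionnaire, so the investigators should confirm that it records residence and whether the woman has given birth before.

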#### Primary outcome measures

This study has two primary outcomes (proportion of ANC use and institutional delivery). The assessment of outcome measures will be conducted starting from phase II data collection time (after the eighth voice message or 4 months from the date of enrollment) and at phase III data collection time (after the 24th voice message or at close-out time off study). All the participants in the trials will be interviewed about their ANC visits and place of delivery by using a structured questionnaire. Antenatal care service use is defined as maternal health care service use during pregnancy. The participants will be considered as an ANC service user if they have at least one ANC visit. Institutional delivery is giving birth at a health facility (Fig. 3).

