### Participants: inclusion and exclusion criteria

The participants will be recruited from two districts (Haramaya and Kombolcha districts) based on pre-set eligibility criteria (pregnancy, gestational age (GA), ownership of a mobile phone and willingness to participate). The participant will be included in the trial if her GA is less than 16 weeks, she owns a mobile phone and has willingness to participate. The potential trial participants will be identified by the field worker-based enrollment criteria. For all eligible participants, the field workers will explain about study by reading the participant information sheets; if the study subjects are willing to participate, written informed voluntary consent will be obtained and baseline data collection will be made.

In this trial, study women who fulfill the enrollment criteria for the study but are critically ill at time of enrollment will be excluded from the study. Critically ill women are those pregnant mothers who unable to respond to interview questions because of illness. In addition, women with any systemic illness during this time will be excluded from the study. Any pregnant women with systemic illness need an special ANC follow- up, which is different from the recommended routine ANC follow -up and this set precondition without effect of treament for good adherence to maternal health care service use. Hence, any pregnant mother with known systemic illnesswill be excluded from this study.

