Published evidence supports the notion that the first ANC visit should be as early as possible in pregnancy, preferably in the first trimester (within the first 12 weeks of gestation) and in a normal pregnancy the protocol for pregnancy care recommends four ANC visits [24]. Hence, appointments for ANC follow-up will be adjusted based on GA with the first ANC visit preferably before 16 weeks of GA, otherwise at 16–24 weeks, the second ANC visit between 24–28 weeks, the third ANC visit between 28–32 weeks and the fourth ANC visit or last ANC visit between 32–40 weeks, preferably near to the EDD to ensure that the appropriate advice and care will be provided to prevent and manage problems such as multiple births (twins or more), post-maturity (which carries an increased risk of fetal death) and fetal mal-presentations. Therefore, based on the maternal enrollment framework criteria for this study, any mother with a GA of “*16 weeks-w*,” where “*w*” is any number of weeks less than 16, then the first voice message, which consists of reminders for the first ANC visit and information about advantage of this visit, will be sent. This voice message will be continued every 2 weeks until the end of the time frame for the first ANC visit which is 24 weeks of GA. Thus, a total of eight plus four voice messages will be sent as reminders for the first ANC visit and information about its advantages. Based on the time frame for the second ANC visit (24–28 weeks of GA), the 13th voice message from the initial message will be a reminder for the second ANC visit and information about its advantages. In this time frame, a maximum of two voice messages will be sent. The third stage of the voice message will be about reminders for the third ANC visit and its advantages. This stage of messaging will start from the 15th voice message and a total of two messages will be delivered. The last stage of voice messaging for ANC visit reminders and about its advantages will be started from the 17th voice message and this will consist of three parts (reminders for the fourth ANC visit, EDD and advantages of the fourth ANC and institutional delivery). A maximum number of voice messages from the date of enrollment and until the 42nd week of GA will be 21 voice messages. After the 21st voice message, the message will be changed to reminders for PNC follow-up and about its advantages. A total of three voice messages will be sent for PNC follow-up reminders and its advantages. Hence, an overall number of voice messages which will be sent for the intervention purpose will be 24. The content of all the messages will be first prepared in English and translated into the local language, “Afan Oromo,” and scripted to a female voice through a smart phone recording. Finally, these messages will be loaded on the mobile phone in voice message form to be sent regularly every 2 weeks at 7:00 a.m. to the intervention group:“Hello, this is voice message from a health center. How are you? We are sending this message to remind you about your first ANC visit. Maternal health care services are given free of any cost. This service will improve your health and your baby’s health. Please, come for your first antenatal care visit before 4 months (16 weeks), otherwise before 6 months (24 weeks) of your pregnancy. When you came for your first ANC service you will have a medical check-up, you will receive TT vaccine (medication that prevents tetanus from you and your baby), and you will also be given iron (element) and folic acid (medication which prevents anemia during pregnancy and promotes normal fetal growth). We are waiting for you to give free maternal health care services. If you have any problem please call to 09x……..”

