Randomized controlled trial studies, which were conducted in Zanzibar, Kenya and Nigeria at different times to evaluate the effect of m-health on maternal health care service utilization, have shown a promising outcome on maternal health care service utilization [16, 28, 32, 33]. However, in all aforementioned investigations the study participants were recruited from health facilities which may not show the effect of m-health on early initiation of maternal health care service use. Thus, for the current study, recruitment and enrollment of the study participants will be conducted at the community level. In addition, this investigation will enroll only those mothers at less than 16 weeks of GA to test the effectiveness of m-health on early initiation of maternal health care service use and its uptake. It is also recognized that m-health is a dynamic issue with the fast transfer in both technology and information literacy for developing countries. Hence, there is a need to examine what works or does not work yet and to establish a standard in this area. Therefore, this mobile-phone-based voice message trial study should generate strong evidence on maternal health care service utilization in resource-limited settings with poor literacy, which can be generalizable to similar populations in various settings.

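### The co-primary ANC outcome counts visits made before enrolment, and women who have already attended are not excluded, so its effect is diluted by an unknown, probably small, share

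*Protocol article*

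**What the plan says.** In the Protocol article, Primary outcome measures, ANC use is one of two primary outcomes, and one visit is enough: "The participants will be considered as an ANC service user if they have at least one ANC visit". The window is the whole pregnancy: "Antenatal care service use is defined as maternal health care service use during pregnancy". The Operational definitions start maternal service utilization at conception: "health care service use from conception to delivery and during postnatal period till 45 days or 6 weeks".

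Eligibility does not refer to ANC already received in this pregnancy. A woman is "included in the trial if her GA is less than 16 weeks, she owns a mobile phone and has willingness to participate". The exclusions are critical illness and systemic illness. Screening and enrollment procedure uses pregnancy, gestational age and phone ownership.

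Trial arm A and the Discussion put the recommended first visit within 12 weeks of gestation, with 24 weeks as the outer limit. The opening series of messages consists of first-visit reminders.

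Earlier service use is touched on at Phase I, where "a baseline survey will be conducted on sociodemographic characteristics and maternal health care service use", and again under Outcome measures as previous experience of maternal care. In the analysis it appears only in the exploratory Sub-group analysis. It plays no part in the outcome rule.

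**The concern.** A woman who attended at 10 weeks and enrols at 14 weeks already has the co-primary outcome. No message can change it, and the first-visit reminders have nothing to act on. Such women are fixed successes in both arms.

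Two consequences follow. With similar shares in the two arms, the ANC risk difference and risk ratio move towards no effect. With different shares, the gap adds to the apparent effect of the messages or subtracts from it.

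This also bears on the trial's stated purpose. The Discussion says of earlier trials that "in all aforementioned investigations the study participants were recruited from health facilities which may not show the effect of m-health on early initiation", and gives early initiation as the reason for community enrolment. An outcome that includes initiation before enrolment partly works against that aim.

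**Working it through.** **Inputs from the Protocol article.** 47% (control) and 60% (intervention), from Sample size determination; these are institutional-delivery rates. Two-sided 5%, 80% power, design effect 1.3 and 320 per arm, from Assumption and hypothesis for sample size calculation. The 34% national figure for ANC by skilled workers (2011 survey) is from Background.

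**Assumptions.** The share q with an ANC visit before enrolment is not given, so a range is used. No ANC planning rates are given, so 47% v 60% is borrowed for women with no prior visit. Losses to follow-up are ignored.

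**The plan's own figure.**
- Pooled proportion: (0.47 + 0.60)/2 = 0.535.
- n = [1.96·√(2·0.535·0.465) + 0.842·√(0.47·0.53 + 0.60·0.40)]² / 0.13² = 229.9 per arm.
- Continuity correction: (n/4)·[1 + √(1 + 4/(n·0.13))]² = 245.04, rounded up to 246.
- 246 × 1.3 = 319.8, so 320 per arm. The stated figure reproduces, but for institutional delivery.

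**Dilution, equal q in both arms.** Control: q + (1−q)·0.47. Intervention: q + (1−q)·0.60. The difference is therefore (1−q)·0.13. Power = Φ(difference/SE − 1.96), with SE = √{[p₁(1−p₁) + p₂(1−p₂)]/n} and n = 320/1.3 = 246.2. Restricted to women with no prior visit, the rates stay at 47% v 60% and n = 320(1−q)/1.3.

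| q | Control | Intervention | Difference (points) | Risk ratio | Power, all women | Power, no prior visit |
|---|---|---|---|---|---|---|
| 0 | 47.0% | 60.0% | 13.0 | 1.28 | 83% | 83% |
| 5% | 49.7% | 62.0% | 12.4 | 1.25 | 79% | 81% |
| 10% | 52.3% | 64.0% | 11.7 | 1.22 | 75% | 79% |
| 20% | 57.6% | 68.0% | 10.4 | 1.18 | 67% | 74% |
| 30% | 62.9% | 72.0% | 9.1 | 1.14 | 58% | 68% |

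Worked row, q = 20%: SE = 0.0433, 0.104/0.0433 = 2.40, Φ(0.44) = 67%. Restricted: 256 women per arm, n = 196.9, SE = 0.0498, 0.13/0.0498 = 2.61, Φ(0.65) = 74%.

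**No true effect, q = 20% (intervention) v 10% (control), same SE formula and design effect.**
- 47% in women with no prior visit: 57.6% v 52.3%, a difference of 5.3 points, risk ratio 1.10. 0.053/0.0448 = 1.18; rejection = Φ(1.18 − 1.96) + Φ(−1.18 − 1.96) = 22%.
- 34% in women with no prior visit: 47.2% v 40.6%, a difference of 6.6 points, risk ratio 1.16. 0.066/0.0446 = 1.48; rejection = 32%.
- With q = 10% v 5%, the rejection rates are 9% and 12%.

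These rejection rates are illustrative. With one district per arm, the between-district variation cannot be estimated, and a design effect of 1.3 does not represent it.

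**The case against.** **The share is probably low.** This stands. Women are found in the community by urine test from 28 days of amenorrhea, so many will be met before any visit. The 34% in Background is an older national figure for the whole pregnancy. If it applied here, q = 30% would leave only (0.34 − 0.30)/0.70 = 6% of the remaining women ever attending. The lower rows of the table are extreme.

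**The power loss is measured against a target the plan never set.** This stands in part. No ANC rates or ANC power are stated. If 47% v 60% were the overall ANC rates, q would already be inside them and no power would be lost against 83%. The ratio would still be diluted: at q = 10% the women without a prior visit would have 37/90 = 41.1% v 50/90 = 55.6%, a ratio of 1.35 rather than 1.28.

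**A false effect is a district problem.** This largely stands. A reader might infer that the outcome rule by itself creates a spurious effect. It does so only if early attendance differs between the districts. Study setting and Randomization and sampling procedure assert similar service coverage, though without an early-ANC figure. With one district and one health center per arm, any district difference can look like an effect, for delivery as well. The outcome rule adds one further channel.

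**Baseline already records service use.** This is true and makes the fix cheap, but nothing carries that record into the primary outcome.

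**Restriction leaves a subset.** This is also true. The subset is defined by a characteristic that precedes the intervention, so comparison by assigned arm is kept. The report is, however, collected after the districts have been allocated.

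**Conclusion.** The definition is flawed, to a moderate degree. Followed exactly, it scores events that no message could have caused, and neither the baseline survey nor the exploratory subgroup analysis corrects this. The ANC risk difference is multiplied by (1−q).

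Under the borrowed 47% v 60%, a q of 5 to 10% costs about 4 to 8 points of power, and restriction recovers about 2 to 4 of them. At q of 20 to 30% the cost is 16 to 25 points and the recovery 7 to 10. All of this rests on an assumed q and on borrowed rates.

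A reader might go further and conclude that the ANC comparison is invalid, or that it is shown to be underpowered. The documents do not support either: they give no pre-enrolment share and no ANC power target, and the size may be small. Institutional delivery, on which the sample size rests, is not affected.

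**What to change.** - At Phase I, record whether any ANC visit in this pregnancy has already taken place, and its date.
- Define the co-primary ANC outcome as a first ANC visit after enrolment, among women with none at enrolment, compared by assigned arm.
- Report the share with a pre-enrolment visit by arm.
- Give the all-participant analysis of any visit in the pregnancy as supportive.
- Leave institutional delivery unchanged, in all participants.

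The cost is one dated item in an existing interview and a reworded definition. Trial status says that participant selection had not started, so both could be in place from the first enrolment. The downsides are a smaller ANC denominator (288 of 320 per arm at q = 10%, 256 at q = 20%) and reliance on a reported visit. That report can be checked against medical records, which the Secondary outcomes section already plans to use for cross-checking primary and secondary outcomes. The change removes one channel of district imbalance only; the weakness of one district per arm remains.
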